## 2. Project description

### Background:

Tobacco use is the world's leading preventable cause of premature death and disease causing over 5 million deaths annually around the globe. The proportion of deaths due to smoking in Kazakhstan in 2004 was 24%, twice the worldwide rate (12.0%) and about 50% higher than the rates in Eurasia and in the Russian Federation as a whole (both 16%) [1]. Tobacco harms the health, the treasury, and the spirit of Kazakhstan. Every year, more than 22500 of its people are killed by tobacco-caused disease. Still, more than 16000 children aged 10-14 years and nearly 2.5 million adults (15+ years old) continue to use tobacco each day [2]. Cigarette smoking also causes reduced health-related quality of life (QoL). Smoking abstinence significantly improves the health-related quality of life among tobacco users before and after smoking cessation (health transition) [3].

To tackle this public health problem, Kazakhstan ratified the Framework Convention on Tobacco Control in 2006. In spite of these efforts, the projected tobacco-related premature deaths in Kazakhstan increased to >50% of all smokers in 2014 [4]. The World Health Organization (WHO) and its member states have set a voluntary global target of a 30% relative reduction in the prevalence of current tobacco use by 2025. This organization provides technical guidance based on six demand-reduction measures of MPOWER such as- monitor tobacco use and prevention policies; protect people from tobacco smoke; offer help to quit tobacco use; warn about the dangers of tobacco; enforce bans on tobacco advertising, promotion and sponsorship; and raise taxes on tobacco. [5]

One of the MPOWER strategies is to offer help to quit tobacco dependence. This effort utilizes different strategies including both non-pharmacological (behavioral counselling) and pharmacological therapies. Currently, it is well accepted that smoking cessation drugs such as Nicotine Replacement Therapy (NRT) are effective and safe in real-world settings. [6]

When a person stops using tobacco, the aim of NRT is to replace the nicotine that the smoker would have been receiving, without the additional harmful elements of tobacco.[7]. With fast acting drugs such as nicotine gum, the nicotine is absorbed through buccal mucosa and reaches peak plasma nicotine concentrations within 15–30 min (as compared to within 1–2 min after smoking) and the blood levels reach a flat peak after about 30 minutes of chewing [8]. On the contrary, trans-dermal patches release nicotine more gradually with peak concentrations within hours after application [9]. As a result, none of the available NRT products deliver such high doses of nicotine as quickly as cigarettes. One implication is that combination NRT (fast-acting form + patch) results in approximately 15% to 36% higher long-term quit rates than a single form of NRT. [7]

Using a nicotine replacement treatment (or other smoking cessation drugs) before a quit attempt while smoking normally is called preloading. A systematic review showed limited evidence that nicotine preloading may be effective, but with unexplained heterogeneity between studies. Some studies suggested that nicotine preloading doubled the likelihood of achieving abstinence, while other studies suggested that preloading had no effect [10]. However, more evidence is needed to determine the effectiveness of preloading combination NRT when compared with standard regimen [7]. This study intends to determine and gather further evidence about the effectiveness of preloading combination NRT among adult smokers of Kazakhstan.

**Research question:** What is the effectiveness of preloaded combination nicotine replacement therapy on smoking cessation?

### 3. Methodology and ethical considerations

#### Objectives:

- To determine the effectiveness of preloaded combination nicotine replacement therapy (NRT) on smoking cessation of tobacco smokers.
- To determine the predictors of smoking cessation among the study participants.
- To determine the change in health-related quality of life due to smoking cessation.
- To determine the perception of treatment adherence among the study participants.

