#### C. Recruitment of participants:

Patients and/or visitors of the hospital will be screened for tobacco use. Those who are known tobacco smokers will be advised to register for cessation services at the tobacco cessation center. The smoking cessation trial aims to recruit 490 participants in each arm. The participants will be enrolled based on the eligibility (all current smokers aged 18 years and above with a motivation to quit). Before randomization, smokeless tobacco users, smoking frequency of less than 10 cigarettes per day, pregnant women, lactating women, patients with recent history of myocardial infarction of less than 3 months, and electronic cigarette users will be excluded from the study. Further to this, randomization will be done to allocate participants to the appropriate study arms. The participant information sheet will be given and explained to the participants by the investigator about the risks and benefits of participating in the trial.

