**E. Primary Outcomes:**

The primary clinical outcome will be the binary smoking cessation; abstinence or non-abstinence assessed at 12 months from the starting point of intervention. Non-abstinence will be defined as self-reported smoking anytime during the intervention or follow up and a positive salivary cotinine test.

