| Health related quality of life                                           | 0-Day, 6 months, 12 months                                                                                                                                                                                                                                                                                                                   | 0-Day, 6 months, 12 months                                                                                                                                                                                                                                                                               |
| Saliva cotinine test                                                     | 0-day, Month- 3, 6, 12                                                                                                                                                                                                                                                                                                                       | 0-day, Month- 3, 6, 12                                                                                                                                                                                                                                                                                   |

**K.Statistical Analysis:** The collected information will be summarized by using frequency and percentage for qualitative data, mean and standard Deviation for quantitative data. To compare the outcome measures, quantitative before and after intervention, paired-t test will be used. If data is not following normal distribution, Wilcoxon Signed Rank test will be used. To compare qualitative outcomes, Chi-square test or Fischer exact test will be used. To compare the difference in outcome measures between two intervention groups, independent sample 't' test will be used. If data is not following normal distribution, Mann Whitney test will be used. The P value less than 0.05 will be considered as statistically significant.

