**Results:** The study shall adopt the "Intention to Treat Analysis" mechanism. If the study has missing data more than 10% of the total sample size as expected during sample size calculation, Pattern-Mixture Model within a mixed-effects logistic regression model for longitudinal dichotomous data will be used. Because of the dichotomous outcome, logistic regression version of the mixed-effects model is applicable. The pattern-mixture effects for drug, time, data pattern and their interactions will be interpreted. Pattern mixture sensitivity analysis using SAS/STAT, missing data analysis will be done using R software, and survival analysis will be used to analyze the variation in smoking relapse over time related to the socio-demographics, smoking history, and treatment-related variables.

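### The quality-of-life objective is worded as an effect of quitting, but neither test stated for quantitative outcomes compares participants by abstinence status

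*Protocol*

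**What the plan says.** The third of the four objectives in the protocol (Section 3, Objectives) is "To determine the change in health-related quality of life due to smoking cessation". The therapy table in Section J schedules health-related quality of life (HRQoL) at "0-Day, 6 months, 12 months" in both arms. HRQoL is not listed among the primary outcomes (Section E) or the secondary outcomes (Section F).

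Section K gives two kinds of test for quantitative outcomes:

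- Before versus after: "To compare the outcome measures, quantitative before and after intervention, paired-t test will be used", with a signed-rank test if the data are not normal.
- Between arms: "To compare the difference in outcome measures between two intervention groups, independent sample 't' test will be used", with a Mann-Whitney test if the data are not normal.

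The Results paragraph that follows adds two models, neither of them for HRQoL. If missing data exceed 10%, a "Pattern-Mixture Model within a mixed-effects logistic regression model for longitudinal dichotomous data will be used". Separately, "survival analysis will be used to analyze the variation in smoking relapse over time".

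Quit status will be known: the primary outcome is "abstinence or non-abstinence assessed at 12 months from the starting point of intervention", and Section J schedules a saliva cotinine test at month 12.

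**The concern.** The objective makes a causal statement about quitting. To answer it, some analysis has to set people who quit against people who did not. No analysis stated in the protocol does this for HRQoL. The paired test compares each person with himself or herself at baseline, whether or not that person quit. The between-arm test compares randomised regimens.

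If the paired change were reported against this objective, any general movement in HRQoL over the year would be credited to cessation. An upward drift could produce an apparent benefit where there is none, and a downward drift could hide a real one. At stake is the answer to one listed objective. The primary comparison of abstinence is not affected.

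**Working it through.** **Inputs from the protocol.** Planning abstinence rates are 47.5% and 27.5%, with 5% two-sided significance, 80% power and 91 per arm before loss to follow-up, rounded to 100 per arm after it (all Section G). Section C states 490 per arm, and Section A states 1:1 allocation.

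**The plan's own figure.** With p̄ = (0.475 + 0.275)/2 = 0.375:

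n = [1.960 × √(2 × 0.375 × 0.625) + 0.842 × √(0.475 × 0.525 + 0.275 × 0.725)]² / 0.20² = 90.8, so 91 per arm.

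This matches Section G. It concerns abstinence only; the protocol states no design figure for HRQoL.

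**Assumptions.** The protocol gives no HRQoL instrument, mean, SD or expected drift. I set the SD of the individual change to 1, let drift (change over time common to everyone) run from 0 to 0.3 SD, and use the normal approximation. The planning rates are 6-month sustained abstinence from a cited study; I use them as stand-ins for 12-month rates. I take N = 200 (100 per arm) and, as the alternative, N = 980 (490 per arm).

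**What the paired test estimates.**

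Mean paired change = drift + (share quitting × effect of quitting) = drift + 0.375 × effect.

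The two terms cannot be separated from this one mean. On the same rates 62.5% of participants are not abstinent. Restricting the test to quitters gives drift + effect, which is still not separable.

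**Probability of significance when quitting has no effect.** P = Φ(d√n − 1.96) + Φ(−d√n − 1.96). For d = 0.2 and n = 200, d√n = 2.83 and P = 0.81. The number of quitters is 0.375 × 200 = 75.

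| Drift (SD of change) | All, N = 200 | Quitters only, n = 75 | All, N = 980 |
|---|---|---|---|
| 0 | 5% | 5% | 5% |
| 0.1 | 29% | 14% | 88% |
| 0.2 | 81% | 41% | >99% |
| 0.3 | 99% | 74% | >99% |

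Drift can also run the other way. With a drift of −0.1 SD and a true quitting effect of 0.3 SD, the mean paired change is −0.1 + 0.375 × 0.3 = 0.01 SD, and the benefit disappears from view.

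**What the between-arm test estimates.** Drift common to both arms cancels, so its false-positive rate stays at 5%. If the arms affect HRQoL only through quitting, the difference is (0.475 − 0.275) × effect = 0.20 × effect. For an effect of 0.3 SD this is 0.06 SD. The standard error is √(4/N): 0.141 at N = 200 and 0.064 at N = 980. Power is about 7% and 16%.

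**A comparison by quit status.** With 75 quitters and 125 non-quitters, the standard error is √(1/75 + 1/125) = 0.146. If drift is equal in the two groups and nothing confounds the contrast, the false-positive rate is 5% at any drift, and power for 0.3 SD is about 54% (0.3/0.146 = 2.05). Quitting is not randomised, so those conditions cannot be taken for granted and adjustment is needed.

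**The case against.** The strongest objection is that Section K is a general list of tests. It does not name HRQoL, does not say which test serves this objective, and does not say whether all participants or only quitters are analysed. A statistical analysis plan that is not shown could add an analysis by abstinence status. This stands as a limit: the protocol does not commit itself to answering the objective with the paired test. It does not remove the point, because the protocol itself sets a causal objective and the tests it states for this type of outcome cannot support it.

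A second objection is that the between-arm test, already planned in the same section, deals with common change over time. That is right, and it should be credited. It answers a different question, though. On Section J's description of the arms it estimates the effect of preloading. Section D describes the control arm as gum alone, and the two sections must be reconciled, but on either description the contrast is between regimens and not between quitters and non-quitters. For the same reason it would be wrong to offer the arm comparison as the causal effect of cessation.

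Two stronger readings are tempting:

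- A reader might infer that HRQoL will rise through recovery because the setting is a cardiac surgery centre. Section C says only "Patients and/or visitors of the hospital will be screened for tobacco use"; it gives no split, does not describe participants as unwell, and excludes recent myocardial infarction. Recovery and regression to the mean are possible sources of drift, not documented features of this sample.
- A reader might infer that the plan is very likely to report a false benefit. That follows only if upward drift of about 0.2 SD or more is assumed. At 0.1 SD the probability is 29% with N = 200, at zero drift it is 5%, and the documents give no basis for choosing among these values.

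**Conclusion.** The concern holds in a limited form. The objective is worded as an effect of cessation, and no analysis stated in the protocol compares HRQoL by abstinence status. A paired change cannot be read as the effect of quitting at any non-zero drift, and the between-arm test sees about one fifth of such an effect on the planning rates.

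That the paired change mixes the two terms is algebra and needs no assumed value. The probabilities are illustrations that rest on the assumed drift, an SD of change of 1, and N = 200; they are higher if 490 per arm applies. The documents do not support saying that the objective will be answered wrongly, only that the stated tests cannot answer it as worded. This is worth correcting, but it touches a listed objective outside the primary and secondary outcomes and leaves the abstinence result intact.

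**What to change.** - Analyse 12-month HRQoL by regression on verified 12-month abstinence, adjusted for baseline HRQoL, arm, and the demographic, smoking and medical-history variables that Section I already collects at baseline.
- Reword the objective so that it asks for the change in HRQoL associated with cessation.
- Report the paired before-after change as description only.
- Keep the planned between-arm comparison, adjust it for baseline HRQoL, and label it as the effect of preloading and not of cessation.

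The cost is one additional model and some rewording. HRQoL at 0, 6 and 12 months and abstinence at 12 months are already scheduled, so no new measurement is needed. The price is a more modest, non-causal claim: quitters may differ from non-quitters in ways that the covariates do not capture.

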#### Methodology:

**A. Trial Design:** This randomized, controlled, two-armed, single-blinded, superiority trial with 1:1 allocation ratio is designed based on CONSORT 2010 Guidelines. This superiority trial intends to gather further evidence that combination nicotine replacement therapy is more efficient than a fast-acting NRT alone.

#### B. Study Setting:

The study will be conducted at the National research cardiac surgery Centre, [name], Nur-Sultan, Kazakhstan. This hospital is a tertiary level facility with more than 200 beds. As part of developing the infrastructure for the study, an exclusive tobacco cessation center will be established in a carpet area of 500-600 square feet in the hospital premises. A full-time psychologist shall provide the counseling services and a qualified medical practitioner shall prescribe the nicotine replacement therapy.

#### C. Recruitment of participants:

Patients and/or visitors of the hospital will be screened for tobacco use. Those who are known tobacco smokers will be advised to register for cessation services at the tobacco cessation center. The smoking cessation trial aims to recruit 490 participants in each arm. The participants will be enrolled based on the eligibility (all current smokers aged 18 years and above with a motivation to quit). Before randomization, smokeless tobacco users, smoking frequency of less than 10 cigarettes per day, pregnant women, lactating women, patients with recent history of myocardial infarction of less than 3 months, and electronic cigarette users will be excluded from the study. Further to this, randomization will be done to allocate participants to the appropriate study arms. The participant information sheet will be given and explained to the participants by the investigator about the risks and benefits of participating in the trial.

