**G. Sample size:**

In a study conducted to find the efficacy of preloading combination NRT over standard combination NRT, 6-month sustained abstinence was 47.5% for the intervention group and 27.5% for the control group with a level of significance of 5%, power of 80% in the two-sided test [15.]. This proportion was considered to calculate the sample size for the current study. Eventually, the sample size was derived at 91 in each arm. By considering a loss to follow up of 10% in each arm, the sample size is 100.1 and hence rounded off conveniently to 100 per arm.

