**H. Randomization, blinding, and allocation concealment:**

When planning a randomized clinical trial, careful caution must be executed in the selection of participants for various arms of the study. Selection and accidental bias may occur when participants are not assigned to study groups with equal probability. Hence, block randomization will be done to obtain the two groups using a computer-generated table. Each block contains four participants in a unique sequence of experimental arm and control arm of 245 blocks. The trial will be single-blinded wherein the participant and the principal investigator will not be aware of the group allocation. Data will be maintained by the senior research fellow. Concealment will be ensured in each participant's group allocation by a sealed envelope with the identity number labeled on the envelope.

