## Budget justification

As shown in details in Appendix C, the total project cost for three years is categorized as follows.

| ITEM                                                 | FUND (USD) |
|------------------------------------------------------|------------|
| Payment to research team                             | 109200     |
| Travel                                               | 14400      |
| Materials and supplies                               | 228400     |
| Equipment                                            | 14600      |
| Publication costs, registration, dissemination costs | 25000      |
| Subcontracts                                         | 9000       |
| Overheads (5%)                                       | 21084      |
| Total                                                | 421684     |

The justification of each item are as follows:

1) Payment to the research team: Our research team consists of MPH graduates/students from NUSOM, Nazarbayev university. Students & graduates of Nazarbayev university will enhance their knowledge in the field of tobacco control & also, they will research publish papers in this area. The payment at this section will be allocated to students /Graduates during their research.

2) Travel: The travel will cover conference expenses of the Investigators.

3) Equipment: The equipment needed to buy for the project is as follows: Portable spirometers, carbon monoxide monitors, sphygmomanometers, and weighing scale, all two each in numbers will be procured. To establish an office setup, furniture & computers will be procured. All the equipment mentioned will be covered under the fund. spirometer & carbon monoxide monitor estimated at 2000 dollars per unit.

4) Materials & supplies: Nicotine patches in the intervention group will be estimated at 120 patches per participant for 16 weeks; 90 patches per participant in the control group for 12 weeks. Nicotine gums are estimated at 600 gums per participant in both the groups. Four saliva cotinine kits are required for each participant at 0, 3 months, 6 months, and 12 months. All the mentioned materials & supplies will be covered under the fund. Nicotine patch is estimated at 8 dollars per piece & nicotine gums at 0.35 dollars per piece. saliva cotinine test at 8 dollars per piece

5) Publication cost: This section will cover the cost of publication (proof reading, charges for color printing etc.) in high ranked journals, if necessary.

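### The protocol gives two trial sizes: sections C and H plan 490 per arm (980 in total), while section G, the only derivation, gives 100 per arm (200 in total)

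*Protocol*

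**What the plan says.** Four places in the protocol bear on the size of the trial.

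- Section C (Recruitment of participants): "The smoking cessation trial aims to recruit 490 participants in each arm".
- Section H (Randomization, blinding, and allocation concealment): "Each block contains four participants in a unique sequence of experimental arm and control arm of 245 blocks".
- Section G (Sample size) takes abstinence rates of "47.5% for the intervention group and 27.5% for the control group with a level of significance of 5%, power of 80% in the two-sided test". It continues "Eventually, the sample size was derived at 91 in each arm" and, after a 10% allowance for loss to follow-up, "the sample size is 100.1 and hence rounded off conveniently to 100 per arm".
- The Budget justification allots 228,400 USD to materials and supplies and gives quantities per participant and unit prices: "Nicotine patch is estimated at 8 dollars per piece & nicotine gums at 0.35 dollars per piece", with saliva cotinine tests at 8 USD each.

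Section A describes a "two-armed, single-blinded, superiority trial with 1:1 allocation ratio", so the figures cannot be different splits of one total.

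**The concern.** Sections C and H agree with each other and disagree with section G by a factor of almost five. All three are current text, and no other passage links the two sizes.

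The figure of 490 cannot be a screening number or an attrition allowance. Section C gives it per arm, section H counts places on the randomisation list, and section G has already added its 10% for loss.

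The two sizes are different trials. They have different detectable effects, different power for the stated effect and different supply needs. The ethics submission, the randomisation list, the drug and test-kit orders and the later report of planned against actual enrolment all need one number. As written, the list would be generated at 4.9 times the size that the calculation supports.

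**Working it through.** **1. Reproduce section G.** Inputs from section G: p1 = 0.475, p2 = 0.275, difference d = 0.20, two-sided 5%, power 80%. The mean proportion is 0.375. With the usual pooled-variance formula and no continuity correction:

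n = [1.960 × √(2 × 0.375 × 0.625) + 0.842 × √(0.475 × 0.525 + 0.275 × 0.725)]² / 0.20²

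= [1.342 + 0.564]² / 0.04 = 90.8, so 91 per arm. This matches the protocol.

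Other common formulas on the same inputs give:

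| Variant | n per arm |
|---|---|
| Unpooled variance | 89 |
| Simple pooled variance | 92 |
| Arcsine | 91 |
| Continuity-corrected | 101 |
| One-sided | 72 (82 with continuity correction) |

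None comes near 490.

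**2. Loss to follow-up.** 91 × 1.10 = 100.1, rounded to 100, as the protocol states. Dividing instead gives 91 / 0.90 = 101.1, so 102.

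**3. Compare the sizes.**

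- Section H: 245 × 4 = 980 = 2 × 490, which agrees with section C.
- Section G: 2 × 100 = 200, which needs 200 / 4 = 50 blocks.
- Ratio: 490 / 100 = 980 / 200 = 4.9.

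**4. What each size delivers.** Evaluable participants after 10% loss are 100 × 0.9 = 90 or 490 × 0.9 = 441 per arm. Power for 47.5% versus 27.5% is Φ[(0.20 × √n − 1.342) / 0.670], using the terms of step 1 (0.670 is the second square root).

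- n = 90: Φ[(1.897 − 1.342) / 0.670] = Φ(0.83), or 79.7%.
- n = 441: Φ[(4.200 − 1.342) / 0.670] = Φ(4.27), above 99.9%.

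Solving the same expression for the treatment rate that gives 80% power against 27.5% yields these detectable differences:

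| Enrolled per arm | Evaluable per arm | Power for 47.5% vs 27.5% | Detectable difference from 27.5% |
|---|---|---|---|
| 100 | 90 | 79.7% | 20.1 points |
| 490 | 441 | above 99.9% | 8.8 points |

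**5. Cross-check against the budget.** Quantities and prices are from item 4 of the Budget justification.

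- Experimental participant: 120 patches × 8 + 600 gums × 0.35 + 4 kits × 8 = 960 + 210 + 32 = 1,202 USD.
- Control participant: 90 × 8 + 600 × 0.35 + 4 × 8 = 720 + 210 + 32 = 962 USD.
- One participant in each arm: 1,202 + 962 = 2,164 USD.
- 100 per arm: 216,400 USD, which is 12,000 USD below the 228,400 USD line.
- 490 per arm: 1,060,360 USD, about 4.6 times that line and about 2.5 times the whole project total of 421,684 USD.
- The line divided by the pair cost: 228,400 / 2,164 = 105.5, so it covers about 105 per arm.

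**The case against.** The contradiction itself has no good rebuttal, and a later analysis plan would not remove it, because the protocol states both sizes. The fair objections concern how far the consequences reach.

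- **Choosing the size after seeing results.** A reader might infer that the team could settle on 200 or 980 once results are known. The documents do not support this. The project timeline closes recruitment on 2023-06-24, and the interim data analysis starts on 2023-07-03. The primary outcome is assessed at 12 months and recruitment opens on 2022-04-01, so no participant could have that outcome before April 2023. Results at 3 and 6 months do accrue during recruitment, but no comparative look is planned in that period.
- **An undefined end of enrolment.** This also goes too far. The timeline gives recruitment a closing date. The target number is what is contradictory, and a calendar window does not settle it.
- **980 as a free option.** Within the stated funding it is not one, as the cost comparison shows. That helps to identify which size was costed, but it does not repair sections C and H.
- **The budget as proof of exactly 100.** It is not. The remaining 12,000 USD is unexplained, and the details sit in an Appendix C that is not in the text at hand. The supportable statement is that the costs fit about 100 per arm and exclude 490.
- **Section G as a clean anchor.** It rounds 100.1 down, and its rates are for 6-month abstinence while the primary outcome is at 12 months. Both are fair caveats. Neither explains 490.

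**Conclusion.** The protocol is wrong as written. Sections C and H plan 980 participants and section G plans 200, and 490 per arm has no derivation anywhere in the document. If 490 were meant, the power statement in section G would not describe the trial. If 100 is meant, the recruitment target and the randomisation list are both wrong.

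The derivation and the costing both point to about 100 per arm, so 490 and 245 look like the unreconciled figures. The document does not say so, however, and the sponsor has to decide.

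The power and detectable-difference figures assume a two-sided 5% normal-approximation test with pooled variance, a control rate of 27.5%, and 10% loss that removes participants from the analysis. The cost comparison assumes that the materials line consists mainly of patches, gum and cotinine kits. The finding is an internal inconsistency. The calculation in section G is sound on its own inputs.

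**What to change.** State one size in sections C, G and H.

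- **If section G stands:** replace 490 with 100 per arm in section C and 245 with 50 blocks of four in section H. Note in section G that 90 evaluable per arm gives 79.7% power. Should the sponsor want the full 91 evaluable per arm, 91 / 0.9 leads to 102 per arm, 204 in total, and 51 blocks of four. By the budget's own prices that costs 102 × 2,164 = 220,728 USD, still within the materials line.
- **If 490 is meant:** replace the calculation in section G with the effect size and power that 490 represents, and reconcile the materials budget with about 1,060,360 USD of patches, gum and kits.

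The first route costs a change of wording and a randomisation list of the right length, with no enrolment beyond what section G derives, apart from four participants if 102 per arm is chosen. The second route needs a new justification and new funding.
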